## Abstract

**Background:**

Males employed in the construction industry have high rates of suicide. Although reasons underpinning this risk are multifaceted, poor help-seeking and stigma are represent major contributors. Males in the construction industry are also exposed to other risk factors for mental ill health and suicide, including unemployment. Sigma-reducing interventions that are accessible and attractive to recently unemployed males in the construction industry could therefore improve help-seeking, and address depression and suicidal behaviour in this population.

**Methods/Design:**

Contact&Connect will use a parallel individual randomized design to evaluate the effectiveness of a multimedia-based intervention aimed at reducing stigma. The intervention consists of a package of 12 brief contact interventions (BCIs) delivered over a six month period. BCIs will direct participants to informational programs and microsites. Content will address three major themes: debunking depression myths and stereotypes, normalisation, and empowerment. Target enrolment is 630 (315 in each arm), each to be followed for 12 months. Eligible participants will be males, between 30 and 64 years, unemployed at the time of recruitment, registered with Incolink (a social welfare trustee company for unemployed members of the construction industry), and own a smart phone with enabled internet connectivity.

**Discussion:**

At present, there are no programs that have been shown to be effective in reducing stigma in the blue-collar male population. Contact&Connect promises to provide a tailored, efficient, and scalable approach to reducing stigma, depressive symptoms and suicidality among unemployed males.

**Trial registration:**

Australian New Zealand Clinical Trials Register ACTRN12615000792527  (date of registration: 30 July, 2015).

**Electronic supplementary material:**

The online version of this article (doi:10.1186/s12889-015-2394-x) contains supplementary material, which is available to authorized users.

## Background

Males in the construction industry are at greater risk of suicide than those in the general working population [1]. The reasons underpinning the elevated risk of suicide among males in the construction industry are multifaceted, but likely involve poor help-seeking and high stigma against mental health issues. Evidence suggests for example that help-seeking rates for common mental health problems, including depression, are consistently lower in males compared to females [2]. Internalised stigma, or self-stigma, [3] and stoicism [4] may represent further barriers to help-seeking in males.

Due to the cyclical nature of construction work, males employed in the construction industry are also more likely to experience periods of unemployment than those in other industries [5]. This represents a further risk factor, as research consistently demonstrates that unemployment is associated with an elevated risk of mental health problems [6] and suicidal behaviour [1]. The experience of unemployment, and subsequent loss of the work-related role, social support, and sense of time structure and activity provided by employment [7], may compound feelings of self-stigma and shame associated with a mental health problem, further contributing to suicide risk. To some extent, the experience of unemployment in the construction industry is normalized, with workers anticipating periods without work as they move from project to project [8].

To date, there have been a limited number of intervention studies addressing stigma, help-seeking and overall mental health of males in the construction industry who have recently experienced unemployment. In 2010, a meta-analysis assessed the effectiveness of interventions on work participation and mental distress for unemployed adults [9]. This review identified just six studies fitting inclusion criteria, none of which were conducted in Australia. One of the reasons for the lack of intervention studies in this area is likely connected to the fact that unemployed workers are difficult to identify and engage. Because the workplace is no longer available as an intervention setting for these individuals, recently unemployed workers no longer have regular face-to-face contact with supervisors and co-workers who could provide social support, identify potential mental health problems, and help with accessing professional help. Given the feasibility challenges of face-to-face interventions for this population, there is a need to address the mental health risks associated with unemployment through different mechanisms, such as online and electronic devices.

Online and electronic interventions have been shown to be effective in reducing stigmatising attitudes towards depression [10], knowledge about evidence based treatment [10], help-seeking from family and friends [11], and symptoms of depression and anxiety [12]. However, their effectiveness in addressing stigma and mental health among males in the construction industry is, as yet, unknown. To address this, we describe the design of Contact&Connect, a parallel group randomised controlled trial designed to assess the effectiveness of a multimedia package of informational and educational resources on mental health self-stigma and mental health literacy in males previously working in the construction industry in the state of Victoria, Australia.

## Methods

### Study design

Contact&Connect is an individual-level two-arm randomised controlled trial (Additioanl File 1). A total of 630 participants (315 in each arm) will be recruited. Simple randomisation using a random numbers table generated by computerised software (Stata for Windows, version 13 [13]) will be used to establish the randomisation sequence. Participants will be allocated to either the intervention or wait-list control group by an offsite researcher working independently from the research team. Owing to the nature of this intervention, neither the participants themselves nor the intervention team will be blind to allocation. However, outcome assessors will remain blind to treatment allocation through the use of unique study identifiers.

### Intervention development framework

An intervention mapping approach [14, 15] will be used to develop and refine the Contact&Connect intervention strategy. We will draw on past research conducted by our industry partner, Incolink, to inform the needs assessment phase of this project and will conduct a matrix evaluation to determine the likely outcomes for behavioural change analysis. Incolink is a state-wide social welfare trustee company that provides financial support for construction workers during the times they are without work. Incolink has the support of unions and employers in the industry, and is well recognised and trusted by workers.

Next, we plan to conduct a focus group session with 20 participants to generate program ideas and intervention materials to ensure these address the requirements for behavioural change as set out in the matrix evaluation. Together with the research team, this focus group will assess the adequacy of and solicit suggestions for optimising: 1) industry/male blue-collar worker relevance and framing; 2) preferred modality of BCIs; 3) BCI frequency and timing; 4) the attractiveness, clarity, and usefulness of the content. BCI design and content with then be refined using focus group findings.

We will then consult with our media partner, Publicity Works, to draft the themes, content, scope, and sequence of the BCIs, and to subject these materials to beta-phase testing with our sub-sample of 20 participants to ensure materials meet the needs and expectations of our participant group. The final two phases of the intervention mapping approach involve rolling the intervention out to our full participant group and undertaking process evaluations to determine efficacy and to review potential mechanisms of attitudinal and behavioural change. As part of these evaluations, we also plan on conducting further qualitative interviews with a random sub-sample of 20 participants to assess perceived usefulness of the intervention materials.

### Study objectives and outcomes

The primary objective of this trial is to evaluate the effectiveness of Contact&Connect, a package of multimedia-based brief contact interventions (BCIs), compared to wait-list, on attitudes and beliefs about depression, help-seeking inhibition, shame, self-blame and social inadequacy at post-intervention (six months) and at 12 months following enrolment. Secondary objectives include the evaluation of this package of interventions on suicidal ideation and depression symptomatology 12 months following enrolment.

Additionally, the degree to which changes in attitudes and beliefs about depression, help-seeking inhibition, and shame, self-blame or social inadequacy mediate changes in suicidal ideation or depression symptomatology will also be assessed.

### Participants

Males between the ages of 30 and 64 years who are registered with Incolink, and who own a smart phone with internet connectivity with adequate data download capacity will be invited to participate. Only unemployed persons contacting Incolink over the three months recruitment procedure will be considered.

Study exclusion criteria includes females, those younger than 30 years or older than 64 years, and those without a smart phone, internet connectivity, or adequate data download capacity, and those with inadequate English language skills.

Written informed consent will be sought from all participants prior to allocation. Ongoing consent will be inferred from participants’ response or non-response to the intervention materials and follow-up questionnaires.

Participants will be allocated to either the intervention or control group by an offsite researcher working independently from the research team.

### Intervention condition

Participants assigned to the intervention arm of this trial will receive a series of 12 informational and educational BCIs delivered to their smart phone over an intervention period of six months. Specific BCIs will target the specific outcomes of the project. Thus, separate BCIs will target knowledge about risk and protective factors for depression and suicide, the importance of social support through connections with friends, family, work colleagues, dispelling myths about mental health problems (in others and the self), and improving knowledge about help-seeking and communication.

Contact&Connect will be delivered to participants’ smart phones via rich text messages with embedded hyperlinks to microsites and other digital resources such as videos and digital wallet cards. These additional resources will provide additional information on stigma, mental health and help seeking, provide links to sources of help whilst encouraging the establishment and maintenance of long-term contact with others. BCIs will be delivered using Whispir^TM^ enterprise edition; an automated and programmable SMS message and communication management system. In addition to allowing multiple types of communication at once, this software will enable us to track participants’ engagement with various BCI materials.

### Control condition

Participants randomised to the control condition will be allocated to a wait-list and will receive the intervention materials in full at the conclusion of the intervention period.

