### Data collection

All participants will complete a baseline electronic survey comprising information on sociodemographic information at the time of study enrolment, knowledge of depression symptoms, attitudes towards those with depression, and stigma, shame, self-blame or social inadequacy. Follow-up surveys will take place immediately post-intervention (six months), and then again at 12 months following enrolment to collect information on changes in knowledge of depression symptoms, attitudes towards those with depression, stigma, shame, self-blame, and social inadequacy and also to assess the impact of the intervention on suicidal ideation and depression symptomatology.

Primary outcome measures will include: scores on the attitudes, beliefs, and help-seeking inhibition subscales of the Depression Stigma Scale (DSS; [10]) and the shame, self-blame and social inadequacy subscales of the Self-Stigma of Depression Scale (SSDS; [16]), and levels of perceived social support from family and friends using the Multidimensional Scale of Perceived Social Support (MSPSS; [17]). Secondary outcomes will include: suicidal ideation as measured by scores on the suicidality subscale of the General Health Questionnarire-28 (GHQ-28; [18]) and depression symptomatology as measured by scores on the Center for Epidemiologic Studies Depression scale-Revised (CESD-R; [19]) and the depression subscale of the Brief Symptom Inventory (BSI; [20]).

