Limitations of this design include the potential confounding influence of reemployment. As reemployment is associated with improvements across a number of health domains, including reductions in mental ill health and depression symptomatology [30], the inclusion of individuals who were reemployed during the study may dilute any effect of the intervention package. However, it would be clearly inappropriate and unethical to request that participants refuse offers of employment during the 12 month intervention and follow-up period. Additionally, as the exclusion of these participants would have serious implications for statistical power, we decided to retain these individuals in all of our analyses. However, our analytic strategy will account for re-employment during the six month intervention period.

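### Controls are offered the full package from month 6, so the 12-month comparison stated against wait-list is one of early versus delayed offer

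*Protocol article*

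**What the plan says.** **Length of the intervention.** Protocol article, Intervention condition: the 12 contacts are "delivered to their smart phone over an intervention period of six months". The Discussion uses the same length when it says that "our analytic strategy will account for re-employment during the six month intervention period".

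**What controls get, and when.** Protocol article, Control condition: those randomised to the wait-list "will receive the intervention materials in full at the conclusion of the intervention period".

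**What is compared, and when.** Protocol article, Study objectives and outcomes: the primary objective evaluates the package "compared to wait-list, on attitudes and beliefs about depression" and the other stigma domains, "at post-intervention (six months) and at 12 months following enrolment". For the rest: "Secondary objectives include the evaluation of this package of interventions on suicidal ideation and depression symptomatology 12 months following enrolment". The section adds that the degree to which changes in the stigma measures "mediate changes in suicidal ideation or depression symptomatology will also be assessed", and gives no time point for this.

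**When data are collected.** Protocol article, Data collection: "Follow-up surveys will take place immediately post-intervention (six months), and then again at 12 months following enrolment".

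Neither the Statistical methods section nor the limitations paragraph of the Discussion mentions that controls are exposed between months 6 and 12. The only limitation discussed there is re-employment.

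**The concern.** The stated comparator is wait-list, but a wait-list group exists only until month 6. After that both randomised groups have been offered the same materials, and they differ in when the offer was made. A 12-month difference between arms therefore estimates the effect of receiving the package early rather than late. It does not estimate the effect of the package against not having it.

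This matters most for suicidal ideation and depression, because the objective names 12 months as their only time point. A null result there could be read as no effect on suicidality when it may only show that controls had caught up. The sample-size section makes no allowance for this: it expects the full fall from 13% to 8%.

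**Working it through.** **1. Timeline from the document**

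| Period | Intervention arm | Control arm | Comparison with unexposed controls? |
|---|---|---|---|
| Months 0 to 6 | 12 contacts delivered | Nothing | – |
| Month 6 survey | Package completed | Not yet exposed, if surveyed before release | Yes |
| Months 6 to 12 | Follow-up | Offered the package in full, pace not stated | – |
| Month 12 survey | Six months after the package | Offered the package up to six months earlier | No |

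The intervention period cannot be read as 12 months. The Data collection section equates post-intervention with six months, and the Discussion names a six-month intervention period.

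**2. The plan's own figures** (Same size and power calculations)

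The conflict in timing depends on neither figure, but both are needed for the illustration. The plan does not state sidedness; two-sided 0.05 is assumed.

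- *Primary: difference 0.73, 226 per group, 90% power.* No SD is given, so 226 cannot be checked. Solving back, d = (1.96 + 1.2816) × √(2/226) = 0.305, which implies an SD of 0.73/0.305 ≈ 2.39.
- *Suicidal ideation: 13% versus 8%, 267 per group, 80% power.* The usual formula gives n = [1.96 × √(2 × 0.105 × 0.895) + 0.8416 × √(0.13 × 0.87 + 0.08 × 0.92)]² / 0.05² ≈ 589 per group; one-sided it gives 464. The stated 267 is not reproduced. That is a separate problem.
- *Expected to remain after drop-out:* 315 × 0.70 = 220.5, taken as 220 per arm.

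**3. Illustration of the dilution**

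Let f be the share of the effect that controls gain by month 12. The document gives no value, so a range is shown. The between-arm difference is multiplied by (1 − f).

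- Primary: power = Φ[0.305 × (1 − f) × √(220/2) − 1.96]. At f = 0.5: 0.1525 × 10.488 − 1.96 = −0.36, so power is 36%.
- Ideation: the control rate is p = 0.13 − 0.05f, against 0.08. With p̄ the mean of the two rates, power = Φ{[(p − 0.08) × √220 − 1.96 × √(2p̄(1 − p̄))] / √(p(1 − p) + 0.08 × 0.92)}. At f = 0.5, p = 0.105 and p̄ = 0.0925: (0.371 − 0.803)/0.409 = −1.06, so power is 15%.

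| f (assumed) | Primary difference | Primary power | Ideation rates | Ideation power |
|---|---|---|---|---|
| 0 | 0.73 | 89% | 13% v 8% | 40% |
| 0.25 | 0.5475 | 67% | 11.75% v 8% | 26% |
| 0.5 | 0.365 | 36% | 10.5% v 8% | 15% |
| 0.75 | 0.1825 | 12% | 9.25% v 8% | 7% |
| 1 | 0 | nothing to detect | 8% v 8% | nothing to detect |

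The primary column assumes that the 0.73 difference, which the plan expects at post-intervention, would persist undiminished to 12 months without crossover. In the ideation column, only the fall below 40% is due to crossover. The gap between the planned 80% and 40% comes from the sample size.

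**The case against.** The best defence is that a wait-list design is legitimate up to the point of crossover and that this trial has a usable comparison there. The six-month survey precedes the controls' exposure, the primary sample size is set for post-intervention, and the Statistical methods section plans intention-to-treat analyses at post-intervention. All of that stands, and it limits the point in four ways.

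- **A reader might infer that the trial cannot answer its secondary questions at all.** The document does not support that. The Data collection section can be read as collecting suicidal ideation and depression at both follow-up surveys, which would give a six-month comparison with unexposed controls. The fault is in the time point named in the secondary objective.
- **A reader might infer that half of the primary outcomes are lost.** Every primary scale is due at both follow-ups. One of two time points is affected, and no scale is lost.
- **A reader might infer that the mediation analysis rests on the 12-month contrast.** Its sentence gives no time point. Its outcomes are those the secondary objective places at 12 months, but that is an inference, and the detail may stand in a fuller document.
- **A reader might infer that both arms are equally treated by 12 months.** The pace of delivery to controls is not stated. If it again took six months, controls would only be finishing at the 12-month survey. Nor is it stated whether the intervention period ends for each participant or for the trial as a whole. With three months of recruitment, a trial-wide end would expose the earliest controls up to about three months later.

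The 12-month contrast also remains a randomised one. It answers a different question from the one stated.

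None of this removes the conflict: the objectives still name wait-list as the comparator at a time when controls have been offered the package. An analysis plan could redefine what is estimated at 12 months, but it could not restore an unexposed control group.

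**Conclusion.** The point holds as a conflict between the Control condition section and the Study objectives and outcomes section. As written, the 12-month comparison is early versus delayed offer. It affects one of the two primary time points and the only time point named for suicidal ideation and depression. The six-month primary comparison is untouched.

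The expected direction of bias, if the package works, is towards no difference. Its size is unknown. Across f from 0 to 0.75, power runs from 89% down to 12% for the primary scale and from 40% down to 7% for ideation. These figures assume two-sided 0.05, 220 per arm, an effect size solved back from the plan's 226, and a primary effect that persists to month 12. They show sensitivity to an assumed catch-up and do not forecast what will happen.

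**What to change.** Reconcile the two sections as follows.

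1. Name six months as the confirmatory between-arm time point for the primary outcomes and for suicidal ideation and depression. State outright that the instruments for the secondary outcomes are in the six-month survey, and that controls complete that survey before the materials are released to them.
2. Label 12-month between-arm results as immediate versus delayed intervention, with no efficacy claim against wait-list. State when and how fast controls receive the materials, so that readers can interpret that contrast.
3. Specify that any mediation analysis of the effect against wait-list uses data collected before controls are exposed.
4. Add control exposure after month 6 to the limitations.

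**Cost.** No added participants. No added surveys or instruments either, if the secondary outcomes are already collected at six months; otherwise their three measures must be added to that survey. The change is more than wording: it moves the stated time point of the secondary objectives and lowers the standing of one primary time point. What is given up is a 12-month efficacy claim against wait-list, which this design cannot support. The shortfall in the ideation sample size is not cured by this change and needs its own correction.

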### Data collection

All participants will complete a baseline electronic survey comprising information on sociodemographic information at the time of study enrolment, knowledge of depression symptoms, attitudes towards those with depression, and stigma, shame, self-blame or social inadequacy. Follow-up surveys will take place immediately post-intervention (six months), and then again at 12 months following enrolment to collect information on changes in knowledge of depression symptoms, attitudes towards those with depression, stigma, shame, self-blame, and social inadequacy and also to assess the impact of the intervention on suicidal ideation and depression symptomatology.

Primary outcome measures will include: scores on the attitudes, beliefs, and help-seeking inhibition subscales of the Depression Stigma Scale (DSS; [10]) and the shame, self-blame and social inadequacy subscales of the Self-Stigma of Depression Scale (SSDS; [16]), and levels of perceived social support from family and friends using the Multidimensional Scale of Perceived Social Support (MSPSS; [17]). Secondary outcomes will include: suicidal ideation as measured by scores on the suicidality subscale of the General Health Questionnarire-28 (GHQ-28; [18]) and depression symptomatology as measured by scores on the Center for Epidemiologic Studies Depression scale-Revised (CESD-R; [19]) and the depression subscale of the Brief Symptom Inventory (BSI; [20]).

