### Statistical methods

Intention-to-treat analyses are planned to compare the effectiveness of the Contact&Connect package of interventions on post-intervention. To account for the presence of missing data at the post-intervention and follow-up assessments, we plan to utilise imputation from the participants’ own responses either prior to and, if available, subsequent to drop-out to estimate likely values for missing variables. Simulation work suggests these two methods demonstrate greatest accuracy, least bias, and least reduction in dispersion as compared to other imputation methods [23].

The efficacy of this intervention on both the primary and secondary outcomes will be assessed using multivariate regression modelling. As we anticipate that some participants may become re-employed during the intervention or follow-up period, analyses will be adjusted for number of days reemployed during the intervention and follow-up period. Analyses will be undertaken in Stata for Windows, version 13 [13].

The intervention will also be evaluated qualitatively *post hoc* for appropriateness, ability to engage participants, and overall impact using a semi-structured interview with a random sub-sample of 20 participants. Interviews will be conducted over the phone within eight weeks of the conclusion of the intervention by trained researchers. Data from these interviews will be analysed thematically using NVivo for Windows, version 10 [24].

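### The baseline survey as listed omits suicidal ideation and depression symptoms, leaving no enrolment value for change, for imputing participants with no follow-up survey, or for baseline adjustment

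*Protocol article*

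**What the plan says.** All places are in the Methods of the protocol article.

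- **Data collection, baseline.** "All participants will complete a baseline electronic survey comprising information on sociodemographic information at the time of study enrolment", followed by "knowledge of depression symptoms, attitudes towards those with depression, and stigma, shame, self-blame or social inadequacy".
- **Data collection, follow-up.** "Follow-up surveys will take place immediately post-intervention (six months), and then again at 12 months following enrolment". These surveys collect changes in the constructs of the baseline list, "and also to assess the impact of the intervention on suicidal ideation and depression symptomatology".
- **Data collection, outcomes.** The primary outcomes include "levels of perceived social support from family and friends using the Multidimensional Scale of Perceived Social Support". The secondary outcomes are the suicidality subscale of the GHQ-28, the CESD-R and the depression subscale of the BSI.
- **Study objectives and outcomes.** The degree to which changes in attitudes, help-seeking inhibition and self-stigma "mediate changes in suicidal ideation or depression symptomatology will also be assessed".
- **Statistical methods.** Missing data are to be filled from participants' "own responses either prior to and, if available, subsequent to drop-out to estimate likely values for missing variables". The only covariate named for the regression is the number of days re-employed.

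**The concern.** The two survey descriptions differ in a specific way. The follow-up sentence speaks of change only for constructs already in the baseline list, then adds suicidal ideation and depression symptoms as a separate purpose. Read plainly, those two are first measured at six months.

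That sits badly with two other parts of the plan. The mediation aim is about change in the secondary outcomes, and change since enrolment needs an enrolment value. The imputation rule relies on a participant's own responses, and before the six-month survey the only possible own response is the baseline one.

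At stake are the mediation aim as worded, the place in the intention-to-treat analysis of participants who never return a follow-up survey, and the precision of the secondary comparisons. A baseline measurement that was not taken cannot be recovered later.

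**Working it through.** The plan gives no figure for this point, so there is none to reproduce. The check is a comparison of the lists, followed by two short calculations.

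**1. Where each outcome is named (Data collection)**

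| Construct | Baseline list | Follow-up list | Role |
|---|---|---|---|
| Attitudes, shame, self-blame, social inadequacy | yes | yes, as change | primary |
| Social support (MSPSS) | no | no | primary |
| Suicidal ideation (GHQ-28 subscale) | no | yes, added | secondary |
| Depression symptoms (CESD-R, BSI subscale) | no | yes, added | secondary |

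No other section says that the last three rows are measured at enrolment.

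**2. What depends on an enrolment value**

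- *Change in ideation or depression since enrolment:* not computable. Mediation can still be modelled on follow-up values.
- *Imputation from own responses,* by pattern of missing surveys:
  - 12-month survey missing, six-month present: an own value exists.
  - Six-month survey missing, 12-month present: an own value exists. Under Control condition, controls receive the materials when the intervention period ends, so their 12-month value comes after that release.
  - Both missing: no own response on these scales exists.
- *Adjustment for the baseline score:* not possible for these outcomes, but also not stated as planned.

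**3. How many participants the imputation gap could reach**

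Inputs: 630 recruited, 315 per arm, 30% drop-out (Same size and power calculations). The timing of drop-out is not given, so the share leaving before six months and not returning is an assumption, ranged from 10% to 30%.

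Number with no own value = share × 630

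- 10%: 0.10 × 630 = 63 (31.5 per arm)
- 20%: 0.20 × 630 = 126 (63 per arm)
- 30%: 0.30 × 630 = 189 (94.5 per arm)

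The top of the range requires all of the assumed drop-out to fall before six months.

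**4. Precision forgone, continuous scores only**

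With baseline/follow-up correlation r, linear adjustment for baseline leaves a fraction 1 − r² of the variance. The documents give no r; 0.5 to 0.6 is assumed.

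- r = 0.5: 1 − 0.25 = 0.75, so 25% is removed
- r = 0.6: 1 − 0.36 = 0.64, so 36% is removed

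**The case against.** The strongest reply is that the lists are a prose summary by construct and not a schedule of instruments. MSPSS is a primary outcome and must be collected, yet it is in neither list. Beliefs and help-seeking inhibition, both primary subscales, are not named as such in either. A condensed article may leave the visit table to the full protocol, and the references to change and to prior responses could mean that baseline measurement was intended. This has force: the article does not prove that the scales will be omitted. It does not remove the point, because the explicit contrast between the baseline and follow-up sentences tells a reader that ideation and depression begin at follow-up, and nothing shown corrects that.

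Several stronger readings are tempting, and the documents do not support them:

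- *The imputation plan collapses for these outcomes.* It does not. The rule also uses later responses, so it fails only for participants with no follow-up value.
- *A planned baseline-adjusted analysis breaks.* None is stated. It is an option lost.
- *The secondary outcomes can only be compared unadjusted.* Baseline sociodemographic and stigma measures are collected and could serve as covariates, and a regression is already planned.
- *The arms cannot be compared fairly.* Randomisation keeps the comparison of follow-up values valid without a baseline. What is lost is precision.
- *MSPSS is a baseline defect.* It is missing from both lists, so it is a wider listing gap.
- *The loss can be stated as an effective sample size.* With 315 × 0.70 = 220.5 per arm, the assumed correlations would give 220/0.75 = 293 to 220/0.64 = 344. But the correlation is not in the documents, and the factor does not carry over to the binary comparison of 13% with 8%, the only secondary comparison for which a power calculation is given.

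**Conclusion.** The point holds in a limited form. As the Data collection section is written, suicidal ideation and depression symptoms have no enrolment value. Three consequences follow:

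- The mediation aim, worded in terms of change, has no starting point for these outcomes.
- Participants with no follow-up survey cannot be imputed from their own responses on these scales. How many is unknown; the range of 63 to 189 rests entirely on the assumed 10% to 30% leaving before six months.
- The gain from adjusting for baseline is unavailable. For the continuous scores this would be 25% to 36% of the variance under the assumed correlation of 0.5 to 0.6.

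None of this invalidates the main between-arm comparison. It should still be settled before enrolment, since the remedy is cheap then and impossible afterwards. If the full protocol already places these scales at baseline, what remains is to correct the listing and state the adjustment.

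**What to change.** 1. In Data collection, state that the GHQ-28 suicidality subscale, CESD-R, BSI depression subscale and MSPSS are completed in the baseline electronic survey, before allocation.
2. Name MSPSS in the follow-up survey content as well.
3. In Statistical methods, adjust each outcome for its own baseline score in the planned regression.
4. If the scales are deliberately left out at baseline, reword the mediation aim in terms of follow-up values and say how participants with no follow-up survey are handled for these outcomes.

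The cost is a few more minutes in a survey that every participant already completes, with a small added burden. The instruments are already chosen, and the Trial status section says that full enrolment has not begun.
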